## Discussion

Oligometastatic disease is a state in which prolonged progression-free survival resulting from metastasis-directed therapy may be achievable in a subset of patients. For instance, in the pivotal trial by Ost and colleagues, around 20% of oligometastatic prostate cancer patients remained disease-free at 2-years follow-up after only MDT [14]. The role of SABR in the setting of metastases is still emerging but the early results for LC are promising. Most clinical trials evaluating efficacy and safety of this technique are retrospective. Furthermore, most have included various radiation dosing, and especially for non-spine bone and lymph node metastases the evidence on which fractionation schedule to use, is scarce. A phase III clinical trial is currently underway, which is comparing schemes of single doses of 24 Gy to hypofractionated doses of three 9 Gy fractions for different types of metastases, including non-spine bone and lymph node metastases [15].

For lymph node metastases of various histologies, the use of SABR generates high LC levels of 80% and more, with acceptable toxicity [16, 17]. However; various fractionation schemes are described in the literature, which range between single doses of 16 Gy and higher to schemes of 10 fractions of 5 Gy [16–23].

When SABR is used for treating non-spine bone metastases, the results are also encouraging. A one-year local control rate of more than 90% is reported in a restrospective analysis of 106 non-spine bone metastases treated with SABR, which is comparable to the results of a prospective study of 85 non-spine bone metastases treated with SABR [8, 24]. In the meantime, these studies showed no grade 3 or greater late toxicities, and very few grade 1 or grade 2 pain flare. A review of Bedard on the use of SABR for non-spine bone metastases reported similar results, but due to the lack of consistency in endpoint definitions, it was difficult to compare outcomes across trials [25].

SABR is also often used for treating metastases from radioresistant tumors like renal cell carcinoma or malignant melanoma. Radioresistance may be overcome with dose escalation, particularly by increasing the dose per fraction [9]. A systematic review of Kothari ea. evaluating the use of SABR found excellent LC rates and low rates of toxicity for intracranial and extracranial metastatic renal cell carcinoma [26]. They reported a weighted one-year LC rate of 86% and grade 3–4 toxicities ranging from 0 to 4%. In the setting of oligometastasized malignant melanoma, there is less clinical data available. Nevertheless, a prospective study showed high rates of complete response and durable metastasis control with SABR for extracranial metastases of malignant melanoma, including bone and lymph node metastases [27]. Both for malignant melanoma and for renal cell carcinoma, LC rates achieved are comparable to those obtained with SABR for other histologies, suggesting a dominant mechanism of in vivo tumor ablation that overrides intrinsic differences in cellular radiosensitivity between histologic subtypes [28].

The concept of a risk-adapted approach for SABR fractionation regimens, using smaller fraction sizes for tumor locations that overlap with organs at risk for toxicity, has gained widespread acceptance. This concept is based on the assumption that fractionation relatively decreases the EQD2 for normal tissues. The results of this dose escalation trial, with increasing dose per fraction, can help to improve the risk-adapted approach for non-spine bone and lymph node metastases. Also important in this regard is the alpha/beta ratio of 10 used in the BED calculations, which is an estimate of the general alpha/beta ratio of tumor metastases. However, the available clinical data support the use of a lower alpha/beta for renal cell carcinoma, breast or prostate cancer, which would lead to a higher BED.

To keep the study protocol accessible to most metastasized patients, there is no limitation on the use of concurrent systemic treatment, but this gives a possible increase in acute or late toxicity.

Even though the data are still not sufficient to be able to routinely recommend SABR, the high LC rates and low toxicity rates observed after SABR in patients with oligometastatic disease and in patients with radioresistant metastases justifies continued exploration of strategies for ablative dose delivery within research protocols. To date, we do not have any clear results that demonstrate the benefit of one type of dose or fractioning over another. The aim of this prospective phase I trial is to establish the optimal regimen of SABR for non-spine bone and lymph node metastases, regarding acute and late toxicity as well as efficacy.

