**Methods:**

The DESTROY-trial is a non-randomized prospective phase I trial determining a regimen of choice for patients with non-spine bone and lymph node metastases. A total of 90 patients will be included in three different treatment regimens. They will be offered stereotactic ablative radiotherapy in 5, 3 or 1 fractions. Dose-limiting toxicity will be recorded as primary endpoint. Acute and late toxicity, local response and local recurrence, and progression-free survival are secondary endpoints. Liquid biopsies will be collected throughout the course of this study from the second fractionation schedule on.

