**Discussion:**

Despite its almost universal use in (oligo-)metastatic patients, the level of evidence supporting radical local treatment in general, and stereotactic radiotherapy in particular, is low. This prospective phase I trial will evaluate different SABR regimens for metastases and the differences in immune-stimulatory effects.

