Apart from the direct effect of SABR on metastases, there is also emerging evidence that this treatment can improve disease control outside the irradiated volume by stimulating the immune response. This could potentially lead to so-called “abscopal” effects, i.e. response in non-irradiated lesions. A variety of mechanisms, such as increasing TLR4 expression on dendritic cells, increasing priming of T cells in draining lymph nodes, and increasing tumor cell antigen presentation by dendritic cells, is responsible for this effect [10]. Again, it is not clear which fractionation schedule elicits the most robust immune response. For instance, in combination with anti-CTLA-4 immunotherapy, different radiation regimens in two carcinoma models growing in syngeneic mice were compared [11]. Marked differences in induction of tumor-specific T cells and of an abscopal effect were observed. Each regimen had similar ability to inhibit the growth of the irradiated tumor when radiation was used alone. The addition of anti-CTLA-4, however, caused complete regression of the majority of irradiated tumours and an abscopal effect in mice receiving a hypofractionated regimen (3 fractions of 8 Gy) but not in mice treated with a single dose of 20 Gy. An additional fractionated regimen (5 fractions of 6 Gy) was tested, which showed intermediate results. This indicates that a specific therapeutic window may exist for the optimal use of radiotherapy as an immune adjuvant.

An interesting measure of DNA damage in circulating tumor cells (CTCs) is γ-H2AX, a biomarker for radiation-induced DNA double-strand breaks [9]. Apparently, DNA exonuclease Trex1 is induced by radiation doses above 12–18 Gy in different cancer cells, and attenuates their immunogenicity by degrading DNA that accumulates in the cytosol upon radiation. Cytosolic DNA stimulates secretion of interferon-b by cancer cells following activation of the DNA sensor cGAS and its downstream effector STING. Repeated irradiation at doses that do not induce Trex1 amplifies interferon-b production, resulting in recruitment and activation of Batf3-dependent dendritic cells [10]. This effect is essential for priming of CD8+ T cells that mediate systemic tumour rejection (abscopal effect). These data suggest a link between the immune-stimulatory effects of radiation and the DNA damage response.

It therefore seems an opportune moment to compare the most commonly used stereotactic regimens regarding toxicity and efficacy.

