### Interventions

A minimum of thirty patients will be included for each dose level. The different treatment regimens and their biological effective doses (BED_10Gy_) and equivalent dose in 2 Gy per fraction (EQD_2Gy_) are presented in Table 2. Calculations for BED_10Gy_ and EQD_2Gy_ are made using an alpha/beta ratio of 10 and 2, respectively. An interval of at least 24 weeks from the first patient treatment to the next patient treatment at each dose level will be respected. In the meantime, more patients will be included in the previous dose level, in an effort to establish the secondary endpoints. In case 1 to 5 patients present with DLT at 6 months after SABR, 30 additional patients will be included at the same dose level.

**Table 2 Tab2:** Fractionation schedules

Level	Fractions	Interval	Dose/fraction	Total	BED_10Gy_	EQD_2Gy_
1	5	48 h	7	35	59.5	78.75
2	3	48 h	10	30	60.0	90
3	1	NA	20	20	60.0	110

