### Time schedule and follow-up

The aim is to recruit the necessary number of patients within a timeframe of 48 months. Follow-up of these patients will be life-long in order to correctly estimate the secondary endpoints (Table 3). Patients are seen centrally by the clinical research physician at 3 and 6 months after SABR. At 6 months, repeated imaging is performed in the study to assess local control. All imaging is considered standard and should minimally include a CT of the irradiated lesion (s) but might also include MRI and/or PET-CT (with whatever relevant tracer) if standard for that malignancy. Reports on acute toxicity will be expected within 2 months after closure of the trial.

**Table 3 Tab3:** Time schedule

	TRIAL PERIOD						FOLLOW-UP		
	Screening visit	Pre-study	During study				Year 1	Year 2	Year 3 till ∞
			Every SABR fraction	Last day of SABR	3 months after SABR	6 months after SABR	Every 3 months	Every 6 months	yearly
Informed consent	x								
Clinical examination	x			x	x	x	x	x	x
Registration of toxicity		x		x	x	x	x	x	x
Registration of QoL		x		x	x	x	x	x	x
Blood sample		x	x	x	x	x			
Imaging						x			

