### Statistical analysis

#### Sample size

For each dose level, a minimum of 30 patients will be included. The maximal tolerated dose will be defined as the dose level below which at least 10 patients present with a DLT at 6 months after SABR.

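### With concurrent systemic treatment unrestricted, non-randomised levels filled in sequence cannot support the promised conclusions on efficacy and immune effect; those differences should be labelled descriptive

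*Protocol article*

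**What the plan says.** **Design.** The abstract states: "The DESTROY-trial is a non-randomized prospective phase I trial determining a regimen of choice for patients with non-spine bone and lymph node metastases". Under Interventions, the next level waits at least 24 weeks, and "In the meantime, more patients will be included in the previous dose level, in an effort to establish the secondary endpoints". Under Time schedule and follow-up, "The aim is to recruit the necessary number of patients within a timeframe of 48 months". Under Sample size, "For each dose level, a minimum of 30 patients will be included".

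**Systemic treatment.** The main Discussion explains that, to keep the trial open to most patients with metastases, "there is no limitation on the use of concurrent systemic treatment, but this gives a possible increase in acute or late toxicity". The eligibility criteria neither limit nor balance such treatment. No drug class is named, so immunotherapy is allowed by implication only.

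**What the trial is meant to show.** The abstract's Discussion says that the trial "will evaluate different SABR regimens for metastases and the differences in immune-stimulatory effects". The Background ends by calling for a comparison of the common regimens on toxicity and efficacy. The main Discussion gives the aim as to "establish the optimal regimen of SABR for non-spine bone and lymph node metastases, regarding acute and late toxicity as well as efficacy".

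**Evidence cited.** For the mouse models described in the Background, "Each regimen had similar ability to inhibit the growth of the irradiated tumor when radiation was used alone". When anti-CTLA-4 was added, most irradiated tumours regressed completely and an abscopal effect appeared with 3 x 8 Gy, but not with 1 x 20 Gy. Five fractions of 6 Gy gave intermediate results.

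**Analysis.** Data analysis names a chi-square test and Kaplan-Meier estimation. Blood is collected from the second dose level on.

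**The concern.** Systemic drugs act directly on RECIST response, on PFS and on circulating cytokines and immune cells. The levels are not randomised and fill at different calendar times. The Background itself says that oligoprogression is becoming more common with newer systemic therapies. The share of patients on an active drug, or starting one around SABR, can therefore differ between levels for reasons unrelated to the radiotherapy schedule.

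PFS is the most exposed. It counts any progression or death, and patients with more than three radioresistant metastases have only the symptomatic lesion irradiated. Their PFS depends largely on lesions that only systemic treatment reaches.

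The stake is the interpretation of the trial. A drug difference could be reported as a fractionation effect, or could hide a real one, and the caveat in the Discussion warns the reader about toxicity only.

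**Working it through.** **1. The plan's own figure.** Three levels of at least 30 patients give 3 x 30 = 90, the total in the abstract. No significance level, power or effect size is stated, so there is no power calculation to reproduce.

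**2. What a level comparison estimates.** Let s2 and s3 be the shares of levels 2 and 3 on an active drug, and d the drug's effect on the outcome, taken as the same at both levels. Then

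observed difference = fractionation effect + (s3 - s2) x d.

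The second term does not shrink as patients are added. If the drug acts differently by schedule, as in the mouse models, equal shares do not solve the problem. With a common share s, the pooled contrast is (1 - s) x (contrast without drug) + s x (contrast with drug), a blend that depends on s.

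**3. Illustration.** The documents give no drug shares or drug effects, so all the inputs below are assumptions except the 30 per level. The fractionation effect is set to zero.

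*Immune marker.* Drug effect 1 SD; shares 20% and 50%.
- Spurious difference: (0.50 - 0.20) x 1 = 0.30 SD.
- Mixing treated and untreated patients inflates the variance: 1 + 0.2 x 0.8 = 1.16 and 1 + 0.5 x 0.5 = 1.25.
- Standard error: sqrt((1.16 + 1.25)/30) = 0.283 SD. Ignoring the mixing gives sqrt(2/30) = 0.258 SD, which is too small.

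*Local response at 6 months.* 50% without and 70% with a newly started drug; same shares.
- Level rates: 0.50 + 0.20 x 0.20 = 0.54 and 0.50 + 0.50 x 0.20 = 0.60.
- Spurious difference: 6 percentage points.
- Standard error: sqrt((0.54 x 0.46 + 0.60 x 0.40)/30) = 0.128, or 12.8 points. The bias is 6/12.8 = 0.47 standard errors.
- An unadjusted two-sided 5% chi-square test (exact calculation) would reject in 7.6% of trials with 30 per level, and in 10.6% with 60 per level, a size reachable through the 30-patient expansion under Interventions.

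*Range.* Share differences of 10 to 40 points give 0.1 to 0.4 SD and 2 to 8 points of response.

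**4. More extreme assumptions.** With outcome rates off/on drug of 40/60%, 40/70% or 30/70%, and shares of 30 vs 50%, 20 vs 60% or 10 vs 70%, the same test rejects in 6.3% to 47.3% of trials at 30 per level and 7.8% to 77.0% at 60. The top values need 30/70% outcome rates and a 10 vs 70% imbalance.

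**The case against.** The trial is openly a non-randomised phase I study with a toxicity primary endpoint, and the open drug policy has a stated reason. Histology, site and number of lesions limit attribution too. No immune endpoint appears under Objectives, samples are collected for biobanking, and the assays are described as possible. The chi-square sentence follows toxicity incidence and names no between-level test of response or PFS. All of this is correct. What remains is that the article still states a conclusion on efficacy and immune effect as its aim, and that its one caveat about drugs stops at toxicity.

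A reader might infer more than the documents support:

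- *That drugs go unrecorded, because Table 3 has no row for them.* Table 3 is a condensed schedule that also lacks rows for histology and performance status, both needed for eligibility. The case report form is not shown.
- *That the Background proves an interaction between the trial's own schedules.* The mice received 3 x 8 Gy or 1 x 20 Gy; level 2 is 3 x 10 Gy. The evidence makes an interaction plausible and shows nothing about patients.
- *That the bias is large.* The response example lies well below one standard error and the marker example barely exceeds one; at the lower end of the range it does not.

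The sample at simulation helps with drugs continued unchanged, through change from baseline. It does not help with newly started drugs or with an interaction. Adjustment in an unseen analysis plan could not restore balance, and would be weak with about 30 mixed-histology patients per level.

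**Conclusion.** The point stands as one of attribution and wording. As designed, the trial can describe local response, PFS and immune readouts at each level, but it cannot assign differences between levels to fractionation. The immune contrast is confined to levels 2 and 3. Direction and size cannot be known from the documents: the 0.30 SD and 6-point figures rest on assumed drug shares and effects, and are modest against their standard errors at 30 per level. The conclusion does not depend on them. It follows from unrestricted drugs, no randomisation, sequential filling and a stated aim that goes beyond toxicity. The change is worth making because it is cheap and because, read as written, drug mix could be taken for a fractionation effect.

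**What to change.** 1. Keep the open policy on systemic treatment. Eligibility and treatment do not change.
2. Extend the caveat in the main Discussion from toxicity to local response, PFS and immune readouts.
3. Reword the aim in the abstract's Discussion and in the closing paragraph of the main Discussion: between-level differences in efficacy and immune effect are descriptive, and the choice of regimen rests on toxicity, the primary endpoint. The existing toxicity caveat continues to apply to that choice.
4. Present local response, PFS and immune readouts per level by systemic treatment at SABR: none, continued unchanged, or newly started or changed, with immunotherapy flagged.
5. Confirm that the case report form captures drug class and start and stop dates; add the fields if it does not.

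The cost is a few sentences, some stratified tables and possibly a few form fields. The downside is small groups: at a 20% share, about 6 of 30 patients (0.20 x 30), so intervals will be wide. The tables show the confounding and do not remove it.

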## Abbreviations

BED: Biologically effective dose
cfDNA: Circulating free DNA
CPT: Cellular preparation tubes
CTC: Circulating tumor cell
CTCAE: Common toxicity criteria for adverse events
CTV: Clinical target volume
DLT: Dose-limiting toxicity
DMSO: 10% dimethyl sulphoxide
EDTA: Ethylenediaminetetraacetic acid
EQD2: Equivalent dose in 2Gy per fraction
FBS: Foetal bovine serum
GTV: Gross tumour volume
LC: Local control
LR: Local recurrence
MDT: Metastasis-directed therapy
MTD: Maximum tolerated dose
OAR: Organ at risk
PBMC: Peripheral blood mononuclear cells
PFS: Progression-free survival
PRV: Planning organ at risk volume
PTV: Planning target volume
RECIST: Response evaluation criteria in solid tumours
SABR: Stereotactic ablative radiotherapy
